#### The Randomized Controlled Trial

We implement a rigorous RCT design using pre- and postintervention data coming from online self-administered questionnaires. The sample must be of at least 500 students at the University of Bordeaux. We estimated a sample size of 500 participants for the 2 arms: statistical power=.80, Cronbach α=.05, Cohen *d*=0.5, and 40% attrition with a 2:1 allocation ratio for the intervention group.

At study entry, the 500 students complete the online baseline questionnaire. Among them, 250 students play the EscapeCovid Game while 250 students receive an email with tips and resources for managing their stress during the COVID-19 pandemic. Participants are randomized so that the 2 groups are similar in terms of sex, age, and field of study (stratified balanced randomization). Participants are informed from the beginning of the study that they can be allocated to either the intervention of interest or the comparator. We tell students in the control arm that they are in a waiting list and that they can play the game once the experiment is concluded.

Inclusion is stopped when at least 500 participants have completed at least 3 quarters of each questionnaire, and 250 have played the game until the end. The statistician and the project manager of the EscapeCovid study are in charge of generating the random allocation sequence, enrolling participants, and assign them to one of the 2 arms.

Briefly, the 250 students of the intervention arm (1) complete the online baseline questionnaire, (2) play the EscapeCovid Game at their home within the week after the online baseline questionnaire—a link to the game is given at the end of the questionnaire, and (3) complete the same online questionnaire of the baseline plus some items on the appreciation of the game (satisfaction survey) 2 days after having played the game. After some tests with Tricky staff, the game duration is estimated at about 2 hours, from the online registration with the creation of an account, until the end of the debrief. Instructions to connect and play online are provided in an email sent by the start-up to the student of the intervention arm 2 days before the game session.

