The 250 students of the control arm will (1) complete the baseline online questionnaire, (2) receive the same day an email with tips and resources to manage their stress during the COVID-19 pandemic, and (3) complete the same internet-based questionnaire of the baseline 2 days after having received the email with tips and resources.

Students can complete all steps of the evaluation from anywhere using a smartphone or a computer. However, they can play the game exclusively from home, considering the need for a stable internet connection and a performance computer.

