#### Data Collection Tools

The pre and postintervention questionnaires are administered through the Sphinx software (Georg Brandl) distributing surveys on all media (web, smartphone, QR code, and SMS). The data are automatically imported in a Microsoft Excel file.

The first questionnaire is composed of 112 items. It includes validated scales measuring mental health literacy (French Mental Health Literacy Scale [MHLS-FR]) [18], beliefs about mental health (Health Belief Model [HBM]) [19], emotions (Plutchik’s wheel of emotions) [20], Coping Strategies (Ways of coping questionnaire) [21], Depression (Patient Health Questionnaire-9 [PHQ-9]) [22], Anxiety (Generalized Anxiety Disorder-7 Scale [GAD-7]) [23], Stress (Perceived Stress Scale [PSS4]) [24], and Help-seeking actions (Kessler Psychological Distress Scale in help-seeking youth [K6]) [25]. Sociodemographic information (email address, gender, date of birth, field of study, year of study, and self-perceived health) are also collected to assess the representativeness of the sample (stratifications by sex, age, field of study etc). A question specifically asks the gender giving students the possibility to indicate whether they belong to the LGBT (lesbian, gay, bisexual, and transgender) category (considering the confidentiality of this data). The question of gender as a determinant of mental health will be important to analyze the results considering this confounding variable if the number of individuals is sufficient. The questionnaire is developed by several researchers through different stages of drafts and reviews, following a structured survey construction method in 5 steps [26]. Operational staff members from the team of the coordinator and a group of students pretest the questionnaire for readability, comprehensibility, and face validity. The response modalities are varied: multiple choice, binary responses, Likert scales, and visual analog scales. Mental health indicators and appreciation and relevance results are the main outcomes of the study. All items provided the nonresponse option “not applicable,” “I don’t know,” and “I do not want to answer.” Respondents are required to select an option from a predefined list. The questionnaire is not validated if at least one question is not answered. Respondents are not able to review and change their answers, but they can ask the principal investigator for a document with exclusively their answers. Corrections cannot be made manually in the database in order to avoid any further error.

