#### Quantitative Data Analyses

For the data from the RCT, we will compare the answers between exposed and nonexposed students (intergroup) and measure the change in their answers within the intervention group before and after playing the game and debriefing (intragroup). Our primary analysis will be based on intention-to-treat at the individual level using linear regression comparing the outcomes of the intervention and the control arm. We will measure our primary outcomes in terms of absolute scores and as a percentage of the total possible score. We will control baseline covariates: (1) gender, (2) age, (3) field of study, (4) year of study, and (5) self-perceived health. We will analyze the data from all participants only if at least 3 quarters of the questions are completed. We consider that some users will not go through all questionnaire pages. Missing values will be imputed by replacing them with the mean or median values of the dataset at large, or some similar summary statistics.

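### For the scales measured before and after, the primary between-arm regression omits the baseline score of the same scale, which costs precision but does not bias the comparison

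*Protocol article*

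**What the plan says.** All of this is in the Methods of the protocol article.

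- **Design** (The Randomized Controlled Trial): "We implement a rigorous RCT design using pre- and postintervention data coming from online self-administered questionnaires". The game arm repeats the questionnaire 2 days after playing. Controls "complete the same internet-based questionnaire of the baseline 2 days after having received the email with tips and resources".
- **Scales at baseline** (Data Collection Tools): "It includes validated scales measuring mental health literacy (French Mental Health Literacy Scale [MHLS-FR"), together with scales for beliefs, emotions and coping, and the PHQ-9, GAD-7, PSS4 and K6. The second questionnaire repeats these, drops the sociodemographic items and adds the appreciation and relevance items. The latter also count among the main outcomes but have no pre-test.
- **Primary model** (Quantitative Data Analyses): intention to treat, "using linear regression comparing the outcomes of the intervention and the control arm".
- **Covariates** (same section): "We will control baseline covariates: (1) gender, (2) age, (3) field of study, (4) year of study, and (5) self-perceived health".
- **Stated use of the pre-test** (same section): to "measure the change in their answers within the intervention group before and after playing the game and debriefing (intragroup"). No matching analysis is named for the control arm.
- **Randomisation** (The Randomized Controlled Trial): the arms are to be "similar in terms of sex, age, and field of study (stratified balanced randomization"). Baseline scores are not balanced by design, and the stratifier is sex while the covariate list has gender.

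**The concern.** A score on the same scale taken only days earlier is usually the best single predictor of the post-test score. Here it is available in both arms at no further cost, yet the enumerated adjustment set leaves it out. The between-arm estimate is then less precise than the data allow. A chance difference in baseline scores, which the stratification does not control, carries straight into the estimate.

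The pre-test is instead directed to a change within the game arm. That change contains any game effect plus whatever moves scores on a second completion of an identical questionnaire or over the intervening days. Without the control arm's change beside it, these parts cannot be told apart.

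Precision matters in this trial. The Discussion calls recruitment its hardest challenge, and Future Directions makes commercial roll-out depend on the results showing an impact.

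**Working it through.** **Inputs from the article.** Power 0.80, alpha 0.05 (taken as two-sided), d = 0.5, 40% attrition, N = 500. At 4 November 2024, 23 had played the game and 53 were in the control arm.

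**Assumed.** Pre-post correlation r = 0.3, 0.5 or 0.7 (not in the article); equal SDs at both times; a normal approximation.

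**1. The plan's own sample size.** For an unadjusted comparison of two means with 1:1 allocation, n per arm = 2 × ((1.960 + 0.842)/0.5)² = 62.8, so 63 per arm and 126 in total; 126/0.6 = 210. With the stated 2:1 ratio, the figures are 48 + 96 = 144, and 144/0.6 = 240. Neither gives 500. That is a separate matter. Here 500 only sets the base: 500 × 0.6 = 300 completers, or 150 per arm when split equally as in the 250/250 description.

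**2. Effect of adding the baseline score.** The residual variance is multiplied by 1 − r² and the standard error by √(1 − r²). The detectable effect at 80% power is 2.802 × √(2/150) × √(1 − r²) = 0.323 × √(1 − r²).

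| r | 1 − r² | SE factor | SE reduction | Detectable d, 150 per arm | Unadjusted completers equivalent to 300 |
|---|---|---|---|---|---|
| none | 1 | 1 | – | 0.323 | 300 |
| 0.3 | 0.91 | 0.954 | 5% | 0.309 | 330 |
| 0.5 | 0.75 | 0.866 | 13% | 0.280 | 400 |
| 0.7 | 0.51 | 0.714 | 29% | 0.231 | 588 |

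These gains are upper bounds: they compare against a model whose other covariates explain nothing, and self-perceived health may already recover a little.

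**3. Where the gain matters.**

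- *Planned effect, full recruitment.* At 150 per arm, unadjusted power for d = 0.5 is already 99% (98% for 100 against 200). The planned target is not at risk.
- *Smaller effect.* Power for d = 0.25 at 150 per arm rises from 58% to 62%, 71% and 86% at r = 0.3, 0.5 and 0.7.
- *Shortfall.* If 23 and 53 are read as completers (an assumption), the standard error of d is √(1/23 + 1/53) = 0.250. Unadjusted power for d = 0.5 is about 52%, rising to about 56%, 64% and 80%.
- *Larger base.* The stopping rule asks for 500 questionnaire completers and 250 who have played. At 250 per arm the unadjusted detectable effect is 0.251, falling to 0.239, 0.217 and 0.179 (0.251 × the SE factors).

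**4. If the regression were on change scores.** The variance relative to an unadjusted post-test comparison is 2(1 − r): 1.4, 1.0 and 0.6 at r = 0.3, 0.5 and 0.7. Baseline adjustment gives 0.91, 0.75 and 0.51, which is smaller each time.

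**The case against.** **The article is condensed and an unseen analysis plan may add the baseline score.** That is possible. But the article does not leave the adjustment set open; it enumerates five covariates. A plan that follows the list omits the pre-test.

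**The dependent variable is not defined and could be change.** This stands as an ambiguity. However, the article speaks of change only for the within-arm analysis, and step 4 shows that a change-score model would be less precise than baseline adjustment over this range.

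**A reader might infer a significance test in the game arm, and so a false claim of benefit.** The text does not support this. It plans to measure a change and states no test, p-value or efficacy claim. The primary analysis is between arms, and the first hypothesis is comparative. Only if someone did apply a paired test would false-positive rates be relevant. With 150 pairs, no game effect and an assumed common shift of 0.1 SD, it would be significant in 18% to 35% of trials for r from 0.3 to 0.7; at 0.2 SD, in 54% to 89%. Those shifts are not in the article. Nor is regression to the mean an obvious contributor, since the inclusion criteria set no score threshold.

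**A reader might also infer that the treatment estimate is biased, or that every outcome has an unused baseline.** Neither holds. Randomisation protects the comparison on average, and appreciation and relevance are measured only afterwards. Selective drop-out is a different problem from chance imbalance, and a baseline covariate does not by itself cure it.

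**The design is large enough anyway.** True for d = 0.5 at full recruitment, as step 3 shows.

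**Conclusion.** The point holds for the scales repeated at pre- and post-test: mental health literacy, beliefs, emotions, coping, PHQ-9, GAD-7, PSS4 and K6. As written, their between-arm analysis leaves out the scale's own baseline, and the one stated use of the pre-test is an uncontrolled change that cannot be attributed to the game.

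The cost is a standard error larger than it need be and uncorrected chance imbalance, not bias. The size depends on a correlation that the article does not report. The short retest interval makes a fair correlation plausible, but at r = 0.3 the gain would be slight. The change is worth making chiefly as insurance against a smaller true effect or a recruitment shortfall.

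**What to change.** - For each repeated scale, regress the post-test score on arm, the baseline score of that scale, the randomisation strata as used (sex, age, field of study) and the other listed covariates. State that the dependent variable is the post-test score.
- Analyse the appreciation and relevance items without a baseline term.
- Report before-after change descriptively for both arms, and base any claim of effect on the between-arm estimate.

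This takes a few lines in the analysis plan and no new data. It should be fixed before outcome data are compared by arm. The article reports recruitment as still under way, so there was time to do so. The practical cost is that the baseline and post-test questionnaires must be linked for each participant, which the planned before-after analysis already requires in the game arm.

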Finally, a maximum of 5 reminders will be sent through email to all 500 participants for the completion of the second questionnaire. For the intervention group, an additional maximum of 5 reminders will be sent to schedule a game session and eventually play the game. An additional maximum of 5 reminders will be sent to the students randomly selected to be interviewed. If after the 5 reminders per phase of the study, the student does not reply, we will proceed with the invitation of new students from the contacts we have from the University and attached associations.

The participation to the study is completely voluntary and all students are rewarded with a €20 (US $21.59) gift card.

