### Study Population

The recruitment started in December 2023.

As of November 4, 2024, a total of 191 students have answered the baseline questionnaire and have been randomly assigned to one of the 2 arms, 90 intervention versus 101 control. A total of 23 students have played the EscapeCovid Game (intervention arm) and 53 are in the control arm. Specifically, 54% (103/191) of the participants at the baseline are students in health care disciplines; 11.5% (22/191) in sciences and technologies; and the remaining participants study other subjects 34.5% (66/191) including psychology, law, and so on.

Concerning qualitative data, 20 students (10 for each arm) have been interviewed on the appreciation, relevance, and acceptability of either the game or the email. Students of the game arm were between 18 and 28 years of age. There were 9 females and 1 male. Their year of study ranged from the first year of their bachelor’s degree to the first year of their doctoral studies. Fields of study included medicine, chemistry, physics, biology, sociology, speech therapy, and political science. Students of the control arm were between 18 years and 28 years old. Their year of study ranged from the second year of their Bachelor’s to the third year of their doctoral studies. Fields of study included medicine, physics, nursing and marketing.

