## Discussion

### Principal Findings

This paper outlines the protocol for the evaluation of a cocreated Escape Game on students’ mental health outcomes contributing to prevent and manage mental health diseases and promoting psychological well-being: mental health literacy, appraisal and change of beliefs about mental health, management of emotions, and development of coping strategies. The evaluation is conducted through mixed methods, combining the quantitative results of a RCT with the qualitative results of semistructured interviews.

Concerning quantitative, as of November 4, 2024, the recruited sample is too small to make inferences on the impact of the game. Actually, recruiting students is the hardest challenge of the trial. All along the study, we have observed that the most successful recruitment strategies are: offering gift cards to students completing the whole study (baseline questionnaire, intervention or control arm, and repeated questionnaire); counting on the support of student associations promoting the study among members; and involving professors who present the study during their classes. We will reinforce these strategies to attract and retain students in the trial.

As for the qualitative data, the recruitment of students was far easier and we rapidly interviewed 20 participants by September 2023. The comparison of the responses across the 2 groups, game versus email, showed that gamification improved the retention of messages, especially in terms of recognition and management of emotions. On the other hand, email was considered useful as a memorandum of mental health–related information. In particular, students appreciated the list of available services that they could keep and save for contacting professionals in case of need.

Based on preliminary results, these 2 distinct tools, the EscapeCovid Game, and the informative email, could prove to be mutually complementary in promoting student mental health. By consolidating the specific advantages of each approach while mitigating their respective limitations, we can aspire to a more holistic and informed approach to strengthening psychological well-being within the student community.

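### The primary analysis is labelled intention-to-treat, but the analysed set depends on what students do after randomisation, and the game arm has an extra hurdle

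*Protocol article*

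**What the plan says.** Under Quantitative Data Analyses the label is clear: "Our primary analysis will be based on intention-to-treat at the individual level using linear regression", comparing the two arms. The same paragraph then limits who enters: "We will analyze the data from all participants only if at least 3 quarters of the questions are completed". Missing values are to be filled with the mean or median of the whole dataset, or a similar summary.

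Under The Randomized Controlled Trial, the game arm repeats the baseline questionnaire "plus some items on the appreciation of the game (satisfaction survey) 2 days after having played the game". The control arm repeats it 2 days after an email that goes out on the day of the baseline questionnaire. The end of recruitment is also set there: "Inclusion is stopped when at least 500 participants have completed at least 3 quarters of each questionnaire, and 250 have played the game" to the end.

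Under Recruitment of Study Population, up to 5 reminders for the second questionnaire go to all 500 participants. The game arm gets up to 5 more for scheduling and playing. If, after the reminders for a phase, "the student does not reply, we will proceed with the invitation of new students".

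Under Study Population, 191 students had answered the baseline questionnaire and been randomised by 4 November 2024 (90 game, 101 control). Progress is given as: "A total of 23 students have played the EscapeCovid Game (intervention arm) and 53 are in the control arm".

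**The concern.** Randomisation makes the arms comparable only if everyone randomised is followed and analysed in the allocated arm. Here a student reaches the analysis by completing enough of the questionnaires. In the control arm nothing is needed to trigger the post-test, because the email arrives automatically. In the game arm the student must first book and finish a session of about 2 hours, and the post-test clock starts only then. The article itself links low participation to the length of the game and its computer requirements (Strengths and Limitations). Those burdens fall on one arm only.

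If willingness to finish is related to mental health literacy, coping or the other outcomes, the two sets of completers differ even when the game does nothing. The imputation rule, as placed, reads as filling gaps within questionnaires that pass the three-quarters rule; it does not bring back students with no post-test. An analysis plan could redefine the analysis set later, but it could not recover post-tests that were never sent. That makes this a data-collection issue as well as a wording issue. The article ties commercialisation of the game to the result (Future Directions).

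**Working it through.** **1. Each rule against the label**

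| Rule | What it depends on | Known at randomisation? |
|---|---|---|
| Three-quarters completion | questionnaire response | Not for the second questionnaire |
| Game-arm post-test date | having played | No |
| Control post-test date | email sent on the baseline day | Yes |
| End of inclusion | completers of each questionnaire, and 250 finishers | No |

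Randomisation follows the baseline questionnaire (Study Population), so non-response in the game phase and the second-questionnaire phase occurs after randomisation.

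**2. Interim progress by arm**

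- Game: 23/90 = 25.6%. Control: 53/101 = 52.5%.
- Difference 26.9 points; SE = √(0.256×0.744/90 + 0.525×0.475/101) = 0.068; 95% CI 13.7 to 40.2 points. Fisher exact p = 0.0002.
- Holding control at 53, 34 of the 90 game students would have to have played before p exceeded 0.05.

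This takes the 53 as students who reached a step comparable to playing. The article does not define that figure.

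**3. Bias under no true effect (illustrative)**

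Assume that a latent normal propensity to complete has correlation r with the outcome (SD 1), and that a fraction p of each arm completes. The completers' mean is then shifted by r·φ(c)/p, where c is the cut-off that leaves p above it.

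- Game: p = 0.256, c = 0.657, φ(c)/p = 0.3215/0.2556 = 1.258.
- Control: p = 0.525, c = −0.062, φ(c)/p = 0.3982/0.5248 = 0.759.
- Bias = r × (1.258 − 0.759) = 0.499r.

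The error rate is the chance that a two-sided 5% z test rejects, with SE = √(1/n₁ + 1/n₂). Two sizes are shown:

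- 250 per arm, if the stopping rule is met: SE 0.0894.
- 39 players and 90 controls, if the interim pace continues. Taking recruitment from the start of December 2023, 11.1 months had passed and 7.8 remained to the end of June 2025. So 23 + 7.8×23/11.1 = 39 and 53 + 7.8×53/11.1 = 90. SE 0.192.

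| r (assumed) | Bias, SD | Error rate, 250/250 | Error rate, 39/90 |
|---|---|---|---|
| 0.1 | 0.05 | 9% | 6% |
| 0.2 | 0.10 | 20% | 8% |
| 0.3 | 0.15 | 39% | 12% |

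**4. Price of a true intention-to-treat analysis**

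If the design effect of d = 0.5 applies to players and 25.6% play, the diluted effect is 0.5 × 0.256 = 0.128 SD. With 250 per arm fully followed, 0.128/0.0894 = 1.43, which gives power of about 30%.

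**The case against.** Several parts of the text soften the problem, and they should be given their weight.

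- **Follow-up of non-players.** A reader might infer that they are barred from the post-test. They are not: second-questionnaire reminders go to all 500 participants. What stands is that the steps give non-players no date for it.
- **Replacement.** A reader might infer that non-responders are struck out and replaced. The text says only that new students are invited. Inviting more students does not breach intention-to-treat; dropping earlier ones would. It becomes a problem in combination with the three-quarters rule and a stopping rule that counts completers.
- **As-treated analysis.** The phrase "we will compare the answers between exposed and nonexposed students (intergroup") might suggest one. The next sentence compares the arms by intention-to-treat, so this is loose wording.
- **Gift card.** A Discussion remark describes "offering gift cards to students completing the whole study (baseline questionnaire, intervention or control arm, and repeated questionnaire"), which might suggest a reward conditional on playing. The Methods say that all students are rewarded. The two places conflict, and no completion-conditional rule is established.
- **Size.** The correlation appears in no document. The model ignores the planned adjustment for five baseline covariates, including self-perceived health. The 250-per-arm error rates apply only if the stopping rule is reached, and the interim pace points to far fewer players. The article does not say how many of the 23 players returned a post-test, and some students may still have been in progress.

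None of this reconciles the intention-to-treat label with the completion rule, the post-test trigger and the stopping rule.

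**Conclusion.** The concern holds for the core contradiction. As written, the plan would compare students who completed enough in each arm, with an extra barrier in the game arm only, under an intention-to-treat label. That follows from the text and needs no assumption.

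The size is conditional. With interim completion fractions and an assumed correlation of 0.1 to 0.3, the bias is about 0.05 to 0.15 SD. The 5% error rate becomes about 9% to 39% with 250 per arm, or about 6% to 12% with 39 players and 90 controls. The interim gap between arms is unlikely to be chance if the 53 is comparable to the 23, but that is not stated.

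A reader might go further and conclude that motivated students are over-represented among players and that the game will look better than it is. The documents do not support a direction: they give no information on how completion relates to the outcomes, so the bias could run either way.

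**What to change.** (a) Define the primary analysis set as all randomised students, analysed as allocated. Drop the three-quarters rule as a condition of entry, and replace the exposed/nonexposed wording with allocated arm.

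(b) Send the post-test to every randomised student, non-players included, on a date fixed from baseline or randomisation and comparable between arms.

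(c) End inclusion on a fixed number randomised or a fixed date. Keep every randomised student in the allocated arm, and drop the condition that 250 have played.

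(d) Handle missing post-tests with a likelihood-based model or multiple imputation that includes baseline scores, plus a missing-not-at-random sensitivity analysis. This must accompany (a): otherwise the pooled mean or median could fill whole missing outcomes and pull the arms together.

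(e) Label any completer or player comparison as secondary.

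Also reconcile the gift-card statements in Recruitment of Study Population and Principal Findings, and define what the 53 control students had completed.

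The direct cost is protocol and analysis-plan wording, a change to the survey mailing and possibly some extra gift cards. The real cost is dilution: at the interim uptake the intention-to-treat effect would be about 0.13 SD if d = 0.5 holds among players, with power of about 30% at 250 per arm. The protocol should say so openly.

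### Filling missing answers with one pooled mean or median shrinks the estimated effect and makes its interval too narrow, and the three-quarters completeness rule protects no single scale

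*Protocol article*

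**What the plan says.** Quantitative Data Analyses sets the main comparison: "Our primary analysis will be based on intention-to-treat at the individual level using linear regression comparing the outcomes of the intervention and the control arm". It then gives one entry condition, "We will analyze the data from all participants only if at least 3 quarters of the questions are completed", one expectation about respondents, "We consider that some users will not go through all questionnaire pages", and one rule for gaps, "Missing values will be imputed by replacing them with the mean or median values of the dataset at large, or some similar summary statistics". The rule does not separate the arms, baseline from follow-up, items from scale scores, or outcomes from covariates. Its last clause leaves the summary statistic open.

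The Randomized Controlled Trial section uses the same threshold to stop inclusion, once "at least 500 participants have completed at least 3 quarters of each questionnaire". The threshold is per questionnaire in both places.

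Data Collection Tools gives the length of the baseline form, "The first questionnaire is composed of 112 items". It also says "The questionnaire is not validated if at least one question is not answered", and "All items provided the nonresponse option" with three choices, one of which is *I don't know*. These statements do not fully agree with the expectation that some pages will not be reached, so the article leaves unclear how missing values will arise.

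**The concern.** Three features of the stated rule matter.

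- **Pooling.** A value taken from both arms together pulls each arm's mean towards the common mean.
- **Single imputation.** The filled values have no spread, and the model counts them as real observations.
- **A threshold at the wrong level.** Three quarters of a long questionnaire can be complete while a whole scale is empty, and that scale would then be filled entirely with a pooled figure.

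The trial's purpose is to estimate how well the game works on four outcomes, and Future Directions ties deployment and sale to the result. A shrunken effect with too narrow an interval is a poor basis for that. Because the statistic is left open, it could also be chosen after the data are seen.

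**Working it through.** **Plan's own figure.** The article gives no missing share and no figure for the effect of imputation, so there is nothing to reproduce. The missing share below is an assumption, shown as a range.

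**Inputs.** True difference d = 0.5 SD and 40% attrition come from the sample size statement, and 250 per arm from the description of the arms. This leaves n = 250 × 0.6 = 150 per arm. The sample size statement also mentions 2:1 allocation; I use the equal arms described. SD = 1. A share m of scale scores is missing completely at random in both arms.

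**Formulas.** With μ1 and μ0 the arm means and g the pooled mean, the filled arm means are (1-m)μ1 + mg and (1-m)μ0 + mg. Their difference is (1-m)d.

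The standard error from observed values is √(2/[n(1-m)]). After filling, the within-arm variance is about (1-m), so the model reports about √(2(1-m)/n), which is (1-m) times the former. That figure is correct for the shrunken quantity but too small as a standard error for the true effect.

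Coverage follows from the bias, md, relative to the reported standard error: Φ(1.96 - b) - Φ(-1.96 - b), with b = md/SE.

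| m | expected difference | SE, observed values | SE, after filling | b | coverage, formula | coverage, simulated |
|---|---|---|---|---|---|---|
| 2% | 0.490 | 0.117 | 0.114 | 0.09 | 95% | 95% |
| 5% | 0.475 | 0.118 | 0.113 | 0.22 | 94% | 94.5% |
| 10% | 0.450 | 0.122 | 0.110 | 0.46 | 93% | 92% |
| 25% | 0.375 | 0.133 | 0.100 | 1.25 | 76% | 75% to 76% |

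Simulated mean estimates were 0.473 at 5%, 0.447 to 0.450 at 10% and 0.373 to 0.374 at 25%. Analysing only the observed values in the same simulated data gave estimates of 0.50 and 95% coverage throughout.

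**Unequal missingness.** With shares m1 (intervention) and m0 (control), and w the intervention share of observed values, the expected difference is d[1 - m1(1-w) - m0w]. For 25% and 10%, w = 112.5/247.5 = 0.455, giving 0.5 × (1 - 0.136 - 0.045) = 0.41. Simulated coverage was 87%.

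**Effect on the test.** Estimate and standard error shrink together. Simulated power at 25% missing was 0.962 with filling and 0.963 with observed values only. With no true effect, the rejection rate at 25% missing in both arms was 5.1%.

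**Whole scales.** A quarter of 112 is 28 items. PHQ-9, GAD-7, PSS4 and K6 hold 9 + 7 + 4 + 6 = 26, reading the counts from the scale names. All four could therefore be empty on a baseline form that still passes.

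**The case against.** The strongest reply is that little may be missing. A form with an unanswered question is not validated, and participants below three quarters are left out, so gaps may come only from the nonresponse choices. At 2% to 5% the table shows almost no harm. This stands as a limit on the size of the problem. It does not remove the problem, because the same article expects respondents who stop before the last page and gives no missing share.

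It can also be said that the test is nearly unaffected and the bias is towards no effect. That is right for equal random missingness, but the trial will also report effect sizes and intervals.

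The four-scale example has limits too. Those scales are not the four hypothesised outcomes, the count is for the baseline form, and the length of the second form is not given. The example shows what the threshold permits; it does not predict what will happen.

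A reader might infer more, in three ways that the document does not support:

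- **That 25% is the most any outcome can lose.** The rule caps each person's share of questions, not the share of people who lack a given scale. A single scale could exceed 25%, and most would probably lie well below it.
- **That *I don't know* means no knowledge, so literacy scores will be inflated.** The items and scoring are not shown, and the article classes this answer as nonresponse.
- **That false positives will rise.** In simulation they did so only when the mean also pooled baseline with follow-up, both arms improved and missingness differed by arm: 5.8% with a 0.3 SD improvement and 25% against 10% missing, and 13.6% with 0.5 SD and 40% against 10%. The article does not say that the time points are pooled.

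**Conclusion.** The point holds. As written, the rule biases the estimated difference towards zero by about the missing share and gives intervals that are too narrow for the true effect. This is a rule the article states, not a detail left to an analysis plan, and nothing else in the article repairs it. The size is unknown because the missing share is unknown: negligible at 2% to 5%, noticeable at 10%, and serious at 25%. These figures assume whole scale scores missing completely at random, equally in both arms, with 150 per arm and d = 0.5. They do not show a loss of power or an invalid test. Nor do they describe the planned 40% attrition, because participants who fall below the completeness threshold are excluded and not imputed.

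**What to change.** 1. Delete the pooled mean or median rule, including the clause that leaves the statistic open.
2. Set the completeness threshold for each scale. Score isolated missing items from the respondent's own answered items, or by the scale's published rule; below the threshold, set the scale score to missing.
3. Handle missing scale scores by multiple imputation within arm, using the baseline score, the stratification factors and the listed covariates. Report an analysis of observed values as a sensitivity analysis.
4. State before analysis how *I don't know* is scored on literacy items under the scale's own scoring rules, and do not fill it by default with a pooled mean.

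Data collection does not change. The cost is revised wording, slightly more programming and wider intervals.
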